*Functional activation: cue reactivity:* One of the most prominent models of addiction is incentive sensitization (Robinson and Berridge, 2001), where the brain mesocorticolimbic reward system is sensitized, and drug cues acquire motivational salience and become conditioned reinforces themselves. In the case of smokers, smoking-related environmental stimuli can elicit smoking urges and cravings, which in turn is associated with compulsive smoking and relapse. Most neuroimaging studies examining neural reactivity to smoking-related (compared to neutral) cues have shown that smokers exhibit increased activation in regions involved in reward, craving, emotions, and memory, as well as regions associated with visuospatial attention (Due, 2002), suggesting increased attention to stimuli of heightened attentional salience. One study found that hyper-activation in some of these regions and decreased connectivity with cognitive control networks predicted “slips” in abstinence (Janes et al, 2010), and behavioural and non-nicotinic pharmacological smoking interventions can normalize these brain responses relative to non-smoking controls (Culbertson et al, 2011; Franklin et al, 2011; Westbrook et al, 2013). However, only a small number of studies have examined the effect of varenicline treatment on smoking cue reactivity. Although these studies suggest that varenicline modulates relevant networks, none of these studies used a full 12-week treatment protocol one study only required 3 days of abstinence prior to the second scan (Loughead et al, 2013), and another study required subjects to be non-abstinent even after 3 weeks of medication (Franklin et al, 2011). Our study will address this gap in the literature by conducting fMRI scans at baseline and after 12-weeks of varenicline treatment in both the active and sham treated tDCS groups. The sham tDCS group will allow us to examine the effects 12-weeks of varenicline treatment on cue reactivity in both quitters and non-quitters. Furthermore, we can compare the treatment effects of active versus sham tDCS within-subjects by comparing the pre- and post-treatment scans. Active tDCS should reduce cue-reactivity by increasing plasticity of the left DLPFC.

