**Hypotheses**:

1. The combination of varenicline treatment plus tDCS to the left DLPFC will improve smoking cessation outcomes and relapse rates in treatment seeking smokers.
2. Active tDCS will reduce fMRI BOLD response to smoking cues compared to baseline within-subjects and compared to sham tDCS between subjects. Those who quit smoking in the last 4 weeks of treatment will show a “normalization” of brain reactivity to smoking cues and reward anticipation relative to those who were unable to remain abstinent over the short term due to tDCS extinguishing the salient properties of smoking-related cues and reward anticipation.
3. Compared to baseline, varenicline treatment will reduce within subject attentional bias, as measured by parameters of visual scanning behavior (VSB), to smoking and negative emotional cues.
4. Active tDCS will reduce attentional bias to smoking and negative emotional cues compared to sham tDCS. Those who quit smoking in the last 4 weeks of treatment will show “normalized” attentional bias patterns to smoking cues and reward anticipation relative to those who were unable to remain abstinent over the short term. Subjective measures of cravings will be correlated with within-subject changes in attentional bias to smoking cues and reward anticipation.
5. Individuals with larger changes in attentional bias to smoking-related cues and/or negative emotional cues, and lower measures of attentional bias to high-arousal/high-risk cues will have higher rates of abstinence (less relapse). Attentional bias will be measured by parameters of visual scanning behaviour and through the analysis of visual scanning patterns (sequences of fixations).
6. The probability of remaining abstinent over the long term will be inversely correlated with VSB measures of novelty seeking behavior.
7. Active tDCS will reduce impulsivity compared to sham tDCS as measured by higher delayed discounting scores.

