**Outcome Measures**

The primary outcome measure will be continuous abstinence from smoking during weeks 9 – 12 as reported at clinic visits during those 4 weeks and confirmed using expired CO. Subjects will be classified as treatment responders if they respond “no” to the question: Have you smoked any cigarettes (even a puff) in the last seven days?

The key secondary outcome measures are:

1. Self-reported 7 day point prevalence abstinence throughout weeks 2 to 12 confirmed by expired CO at each clinic visit. To calculate survival curves we will also collect self-reported continuous abstinence weeks 9 through 26. For weeks 13 to 25, this will be collected via email or text message. For week 26, subjects will attend a brief clinic visit so abstinence can be confirmed with expired CO and urinary cotinine using a semi-quantitative dipstick. We hypothesize that the active tDCS group will have higher rates of abstinence (less relapse) than the sham tDCS group.

2. fMRI: change in Blood Oxygen Level Dependent (BOLD) activation in brain regions known to be associated with drug craving and emotion processing/regulation. MRS: GSH levels measured in a single voxel placed over prefrontal cortex. Fractional anisotropy (FA) values will be extracted from DTI analysis from regions of interest (ROIs) or to form probabilistic tractography for the whole brain. Network maps will be extracted and analyzed from the resting state functional connectivity measure.

3. Eye Tracking tests: changes in attentional bias to smoking-related cues and negative emotional cues. Attentional bias to high-arousal/high-risk cues.

*Self-Report Measures*

Participants will complete the 10-item Questionnaire of Smoking Urges-Brief (QSU-10; Tiffany and Drobes, 1991) and the Minnesota Nicotine Withdrawal Scale (MNSW; Toll et al, 2007) at each treatment session upon arrival and immediately after tDCS. They will complete a Side Effects Checklist ([name] et al., 1995) at the end of each treatment session.

Trait scales to be completed at baseline will include the FTND (Heatherton et al 1991) and Alcohol Use Disorders Identification Test (Saunders et al., 1993), 90-day Alcohol Timeline Followback (TLFB; Sobell and Sobell, 1992); 30-day Tobacco Timeline Followback (adapted from alcohol TLFB); Sensation Seeking Scale (Zuckerman et al., 1978).

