**Sample Size and Power Calculation**

If we assume a 40% abstinence rate at end of treatment in the varencline plus sham tDCS group, the abstinence rate in the active tDCS group would need to be double that or 80% in order to see a statistically significant difference with n=25 per arm, p <0.05, and 80% power. As such we do not expect to see a statistically significant difference between the two treatment arms at 25 subjects per arm.

For the treatment part of the study, the main purpose of the study is to establish an Effect Size for tDCS as an adjunct to standard varenicline treatment. This is independent of the number of subjects but allows us to estimate the N that would be required to achieve statistical significance depending on the effect size we observe. The effect size measure we will use will be the partial η2 generated by SPSS and is described in greater detail below.

For the MRI portion of the study, 15 to 25 subjects per group is standard in the neuroimaging field and is more than sufficient to detect significant within- and between-group differences in brain activity.

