**Data Analysis**

Continuous data (cravings, mood, cigarettes smoked/day, CO) will be assessed with 2 Gender x 2 (Laterality) x 10 (session) Analyses of Variance (ANOVA). Parallel ANOVAs will assess self-report measures during post-treatment follow-up. Categorical data (e.g., # abstinent participants/session) will be assessed with chi-square, and Kaplan-Meyer survival analysis for repeated measures. Planned comparisons will be performed for the critical experimental conditions (active tDCS) vs. sham.

The critical metric will be Effect Size (partial η2 generated by SPSS), rather than p level. This will reveal the degree of efficacy for the primary outcome variable, Consecutive Days Abstinent (small = .01, medium = .06, large = .14), and allow us to estimate N required to achieve statistical significance for this effect (80% power, α = .05, two-tailed). Pearson correlations will explore the possible relationship between effects of tDCS (session 10 scores, controlling for session 1) and trait factors (e.g., FTND, age, gender, depression).Analysis of MRI data

For the neuroimaging data, brain imaging measures will be compared between groups and across time points, using analysis of variance. MRI measures will also be related to subjective responses (i.e., baseline scores and changes in craving, mood, and withdrawal) using linear regression.

fMRI data will be analyzed by fitting a general linear model (GLM) to the data time-series at every voxel across the brain (and/or within ROIs) and assessing effects using F/t-tests and % signal change calculations. Quantitative T1 maps and DTI analysis will be analyzed at the whole brain level and using ROIs.

After back-sorting by treatment outcome (achieved/maintained abstinence), we expect baseline measures to predict relapse, and active tDCS treatment to result in more efficient functional activation, . than sham tDCS at the second MRI scan.

Analysis of Eye-Tracking Data

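### The expected active-versus-sham activation difference is stated after sorting by abstinence, a post-randomisation outcome; the unsorted contrast should be named as the tDCS effect

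*Protocol*

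**What the plan says.** Two active-versus-sham imaging contrasts appear under Data Analysis in the protocol.

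- **Unsorted.** "brain imaging measures will be compared between groups and across time points, using analysis of variance". Nothing here depends on quitting.
- **Sorted.** Two paragraphs later: "After back-sorting by treatment outcome (achieved/maintained abstinence), we expect baseline measures to predict relapse, and active tDCS treatment to result in more efficient functional activation". The sentence ends "than sham tDCS at the second MRI scan".

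The second hypothesis keeps the two questions apart. On arms: "Active tDCS will reduce fMRI BOLD response to smoking cues compared to baseline within-subjects and compared to sham tDCS between subjects". On quitters, in its own sentence: "Those who quit smoking in the last 4 weeks of treatment will show a “normalization” of brain reactivity". Outcome Measures gives the expectation for the sorting variable: "We hypothesize that the active tDCS group will have higher rates of abstinence (less relapse) than the sham tDCS group".

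Background and Rationale links brain reactivity to quitting. It cites a study in which "hyper-activation in some of these regions and decreased connectivity with cognitive control networks predicted" slips in abstinence. Under Design and Neuroimaging there are two baseline scans, and the end-of-treatment scan is the third.

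**The concern.** Abstinence is a result of treatment. If tDCS helps people quit, quitters on active tDCS include some who would not have quit on sham, and non-quitters on active tDCS are the most resistant. Comparing arms within quitters or within non-quitters then compares different kinds of smoker. If quit propensity is related to the scan, as the protocol holds, an arm difference can appear when tDCS does nothing to activation, or a real one can be distorted. Any part of the effect that runs through quitting is removed as well. The sorted contrast is also the only one whose expected result is given in the analysis section, so it could be reported as the mechanistic finding.

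**Working it through.** **The plan's own figure.** Sample Size and Power Calculation assumes 40% abstinence on sham and says that "the abstinence rate in the active tDCS group would need to be double that or 80" per cent at 25 per arm, p<0.05 and 80% power. The two-sided pooled formula gives n = [1.96·√(2·0.6·0.4) + 0.8416·√(0.4·0.6 + 0.8·0.2)]² / 0.4² = (1.358 + 0.532)² / 0.16 = 22.3, so 23 per arm. At 25 per arm, power is 84.5% by normal approximation and 78.8% by Fisher's exact test. The figure reproduces and is not in dispute. It is a detectability bound, not a forecast.

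**Inputs.** The 40% and 80% rates and 25 per arm come from the protocol. The 60% rate, the correlation r = 0.5 between quit propensity and lower activation, and the scan-rescan correlation t are assumptions. Propensity z is standard normal, and a participant quits when z exceeds an arm-specific cut-off c. tDCS has no effect on activation. Positive values mean higher activation on active tDCS, that is, against tDCS.

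**Step 1: who is in each stratum.** Mean z is φ(c)/p among quitters and −φ(c)/(1−p) among non-quitters.

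| Abstinence p | Quitters | Non-quitters |
|---|---|---|
| 40% | 0.386/0.4 = 0.966 | −0.386/0.6 = −0.644 |
| 60% | 0.386/0.6 = 0.644 | −0.386/0.4 = −0.966 |
| 80% | 0.280/0.8 = 0.350 | −0.280/0.2 = −1.400 |

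**Step 2: single end-of-treatment scan, activation = −0.5z + noise.**

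- 80% v 40%: quitters −0.5·(0.350 − 0.966) = +0.308 SD; non-quitters −0.5·(−1.400 + 0.644) = +0.378 SD. The weights are 10·20/30 = 6.67 and 15·5/20 = 3.75, so the pooled value is +0.33 SD.
- 60% v 40%: +0.16 SD in both strata.
- 40% v 40%: 0.

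If the 0.5 applies to the baseline scan and a fraction t carries to the final scan, these values are multiplied by t. At t = 0.7 they are 0.7·0.16 = +0.11 and 0.7·0.33 = +0.23 SD.

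**Step 3: using the baseline scan.**

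- Propensity acts only through baseline activation: the change score is biased by (t − 1) times the step 2 value. At 80% abstinence this is −0.3·0.33 = −0.10 SD for t = 0.7 and −0.5·0.33 = −0.17 SD for t = 0.5, now in favour of tDCS. The baseline-adjusted sorted contrast is unbiased.
- Propensity acts only on the final scan: change and baseline adjustment both leave the +0.16 to +0.33 SD in place.

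**Step 4: error rates and power (4,000 simulated trials per setting, single scan, model with arm and quit status).**

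| r | Active abstinence | False-positive rate, sorted | Power for an assumed 0.8 SD reduction: unsorted / sorted / quitters only |
|---|---|---|---|
| 0.5 | 80% | about 20% | 80% / 35% / 25% |
| 0.5 | 60% | about 9% | 79% / 63% / 35% |
| 0.3 | 80% | about 10% | 80% / 48% / 35% |

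The unsorted contrast held 5% in every setting.

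**Step 5: an effect that runs through quitting.** Assume a direct benefit of 0.30 SD and a benefit of quitting of 0.50 SD. The as-randomised difference at 80% v 40% is 0.30 + 0.50·(0.80 − 0.40) = 0.50 SD. Within strata it is about 0.30 SD even when propensity is unrelated to the scan.

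**Step 6: stratum sizes.** At 40% v 80% there are 10 v 20 quitters and 15 v 5 non-quitters. The difference detectable with 80% power is (1.96 + 0.8416)·√(1/n₁ + 1/n₂): 0.79 SD for 25 v 25, 1.09 SD for quitters and 1.45 SD for non-quitters.

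**The case against.** The strongest reply is that the randomised comparison is already planned. The unsorted analysis of variance is in the same section, and the second hypothesis states active versus sham separately from quitters versus non-quitters. The eye-tracking analysis also keeps the two apart. This stands. A reader might infer that the imaging comparison of arms is made only after sorting, and the documents do not support that.

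The sorted sentence is also an expectation, not a model. It names no test, and its punctuation suggests that words were lost. The sorting may have been meant only for the relapse-prediction half. That reading is possible, but the opening clause grammatically governs both halves, so the text needs to say which is meant.

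A reader might also infer that sorting is always biased against tDCS. The study of slips cited in the background points that way for a single scan, but Outcome Measures defines the fMRI outcome as a change, and step 3 shows that the sign can then reverse. It also reverses if the correlation runs the other way. If the benefit is concentrated in quitters (assumed 0.3 SD direct plus 0.5 SD more in quitters), the quitter stratum shows 0.65 to 0.89 SD against 0.70 SD as randomised.

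Lastly, the larger figures use 80% active abstinence, and the protocol says it does not expect a significant difference in abstinence at this sample size. They are an upper scenario.

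**Conclusion.** The point holds in a limited form. The protocol describes two active-versus-sham imaging contrasts and does not say which one is the tDCS effect. The one given an expected result is, as written, conditioned on an outcome that treatment is meant to change, so randomisation does not protect it.

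If abstinence differs by arm (60% to 80% against 40%) and the assumed correlation is 0.5, an unadjusted end-of-treatment contrast is shifted by about +0.1 to +0.3 SD against tDCS. A change score can shift by about 0.05 to 0.17 SD in favour of it. With equal abstinence there is no bias, though the strata remain small. The documents fix neither the direction nor the size. The finding is that the sorted contrast is unreliable as a treatment comparison, not that the trial has lost its randomised one.

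Separately, the sentence places the comparison at the second scan, while Design and Neuroimaging make the end-of-treatment scan the third.

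**What to change.** Split the sentence in Data Analysis into three statements.

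1. The tDCS effect on activation is active versus sham in all randomised participants with an end-of-treatment scan, whatever their abstinence status, adjusted for the baseline scan. Because there are two baseline scans, say which one is the covariate.
2. Sorting by abstinence serves the separate, non-randomised question of whether baseline measures predict relapse, with arm as a covariate.
3. Any arm contrast within quitters or non-quitters is exploratory and is labelled so.

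Reconcile the scan number in this sentence with Design and Neuroimaging.

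The cost is wording only. The scans and software are unchanged, and the quitter and non-quitter figures can still be shown descriptively.

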**ABSTRACT**

**Rationale**: While varenicline on its own is the most effective medication for smoking cessation, long-term abstinence is still relatively poor. The addition of tDCS as an adjunct to pharmacotherapy is a novel approach but one that is grounded in a growing evidence-base.

**Research Question/Objective**: The primary objective of this research is to provide preliminary evidence of the effectiveness of tDCS as an adjunct treatment to pharmacotherapy for smoking cessation. Does the addition of active tDCS to the left DLPFC improve the effectiveness of varenicline in the treatment of tobacco dependence? Does it make individuals more resistant to relapse in the long-term?

**Study Design**: Double-blind, sham-controlled, randomized clinical trial

**Setting**: A free Nicotine Dependence Clinic in downtown Toronto, Canada

**Participants**: Fifty daily dependent adult smokers seeking treatment to quit smoking

**Intervention and Procedures**: Twelve weeks of varenicline treatment plus tDCS (active: 20 minutes at 2 mA OR sham: 30 seconds at 2 mA, 19.5 minutes at 0 mA), daily (M-F) for the first 2 weeks and then every 2 weeks for the next 10 weeks. 2 FMRI scans at baseline and 1 scan at end-of-treatment. Eye-tracking viewing tests will be conducted at baseline, week 4, week 8,end-of-treatment and at 6 months follow up. Follow-ups at 6-months. A monetary delayed discounting task will be performed at baseline, end of treatment and at 6 months follow up.

**Measurements**: Expired CO, self-reported smoking, and subjective craving and withdrawal at each study visit, weekly self-reported smoking status (7day PPA) from end of treatment to 6 months. For fMRI: BOLD activation, perfusion, structural T1 mapping, DTI and functional connectivity. For Eye-tracking: attentional bias to substance-related cues, attentional bias to negative emotional cues and attentional bias to high-arousal/high-risk cues.

**Potential Impact**: For every two smokers who quit, one life is saved from a tobacco-related mortality. Therefore, even a small improvement in smoking cessation treatment effectiveness and long-term abstinence would decrease the prevalence of tobacco-related death and disease and save the health care system billions of dollars.

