**METHODS**

**Design**

This will be a double-blind sham-controlled two-arm randomized clinical trial. Fifty participants will be randomized (1:1) to each arm. Arm 1 will be active tDCS plus varenicline (n=25) and Arm 2 will be sham tDCS plus varenicline (n=25). Treatment duration will be 12 weeks. Subjects will be required to attend an in person assessment visit. They will then be randomized to a condition. Neuroimaging scans (fMRI) and eye-tracking tests will be conducted in all participants at baseline. Participants will undergo two scans at baseline on different days within the same week: one in a satiated state and one in a non-satiated state. The same tasks will be performed at each scan. s. Following the baseline fMRI scans and eye-tracking tests, subjects will start taking the varenicline simultaneous with starting the tDCS regimen whereby they will come to the clinic every day (Monday to Friday) for the first 2 weeks to undergo the stimulation (active: 20 minutes at 2mA, sham: 30 seconds at 2mA and then nothing). Their target quit date will be at the end of this 2 week period. They will return to the clinic every two weeks for the next 10 weeks for a booster tDCS session and to complete questionnaires. Eye tracking tests will be conducted at the end of the fourth and eighth weeks. At the end of the 12-week treatment period they will undergo a third fMRI scan and eye-tracking tests. For the next 14 weeks they will be contacted weekly by e-mail or text message to report on their smoking status as measured by the 7 day point prevalence abstinence question. “Have you had a cigarette, even a puff, in the last 7 days?” At the 6-month time point subjects will be asked to return to the clinic for a brief visit to confirm smoking abstinence using expired CO and urinary cotinine and to complete questionnaires.

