**Neuroimaging**

The fMRI neuroimaging component to this study will attempt to answer several research questions and address some of the gaps in the tDCS literature. Specifically, how does tDCS and/or varenicline alter functional connectivity between PFC and amygdala or insula? Does the magnitude of change predict successful cessation and long-term abstinence? Does active tDCS change the BOLD response to smoking cues and/or emotional cues? What is directionality of this effect?

Prior to MRI scans, participants will be required to complete a training session at least 24 hours prior to their first scan using the mock MRI scanner, a device which stimulates the scanner conditions including the screen-response apparatus. MRI tasks will be explained to participants outside the scanner and they will then be able to complete mock versions of the cue-reactivity and reward anticipation tasks. Participants who cannot appropriately complete the tasks or who demonstrate excessive motion or discomfort in the scanner due to the confined environment will be excluded from participation in the study.

Magnetic resonance imaging (MRI) will take place at the CAMH Research Imaging Centre (GE Discovery MR750 3T, General Electric Medical Systems, Milwaukee, WI) on 3 occasions: 1) at baseline following 12 hours of smoking abstinence (abstinence scan) 2) at baseline within 1 hour of smoking a cigarette (satiated scan) and 3) at end of the 12 week varenicline treatment. Baseline scans will occur within 1 week of each other and the order of satiated and abstinent scans will be counterbalanced to control for possible order effects. During each session, we will measure: 1) functional activation (blood-oxygen-level-dependent (BOLD) response) while subjects perform cue reactivity and reward anticipation task; resting state functional connectivity (rsFC) 3) quantitative T1 mapping (qMRI) and/or 4) Diffusion Tensor Imaging (DTI).

*Measures at rest*

The following measures (rsFC, DTI, qT1) will be collected with the subject at rest, i.e., no task performance will be required. qT1 images will be acquired across the whole brain. Diffusion Tensor Imaging (DTI)

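### Data Analysis expects the active-versus-sham imaging difference at the second MRI scan, which is a pre-treatment scan, and the end-of-treatment scan has no named baseline comparator and no defined smoking state

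*Protocol*

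**What the plan says.** **Scan schedule.** The Abstract gives "2 FMRI scans at baseline and 1 scan at end-of-treatment". The Design section agrees: "Participants will undergo two scans at baseline on different days within the same week", one satiated and one not. It then starts treatment: "Following the baseline fMRI scans and eye-tracking tests, subjects will start taking the varenicline simultaneous with starting the tDCS regimen". Week 12 follows: "At the end of the 12-week treatment period they will undergo a third fMRI scan and eye-tracking tests". The Eligibility Criteria also list two baseline scans and one at the end of treatment.

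**Smoking state.** The Neuroimaging section requires 12 hours without smoking for one baseline scan. It continues with "2) at baseline within 1 hour of smoking a cigarette (satiated scan) and 3) at end of the 12 week varenicline treatment". The order of the two baseline scans is counterbalanced. No smoking state is attached to the third.

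**Analysis.** The Data Analysis section states that "brain imaging measures will be compared between groups and across time points, using analysis of variance". It then gives a directional expectation, after sorting participants by treatment outcome: baseline measures should predict relapse, and active tDCS should do better "than sham tDCS at the second MRI scan".

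**Outcomes.** The key secondary outcomes include change in BOLD activation and "MRS: GSH levels measured in a single voxel placed over prefrontal cortex". The Abstract also lists perfusion among the fMRI measurements.

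**The concern.** The only sentence that ties the directional arm comparison to a particular scan names one taken before any stimulation. An analyst who followed it literally would look for a tDCS effect where none can exist, in data that mix two smoking states.

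Correcting the ordinal leaves two gaps. A change to week 12 needs a baseline, and there are two, deliberately acquired in different smoking states. The week-12 scan has no specified state, although the baseline rules show that the protocol regards state as material. Hypothesis 2 compares those who quit in the last four weeks with those who did not and looks for normalised reactivity. Quitters will have been without cigarettes for weeks, whereas the others may have smoked shortly before the scan. A difference between them could reflect recent smoking as well as any lasting change.

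The last mismatch is smaller: GSH spectroscopy is a key secondary outcome and perfusion a listed measurement, but the Neuroimaging section acquires neither.

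**Working it through.** The point rests on scan order and timing, so most of the check sets sections side by side. The protocol gives no sample size or power figure for the imaging contrast to reproduce. The 40% and 80% abstinence rates and 25 per arm, from Sample Size and Power Calculation, serve below only as illustration; 80% is the rate the protocol says would be needed for significance, not a forecast.

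**Step 1. Which scan is the second?**

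| Scan, in time order | Timing | Treatment received | Smoking state |
|---|---|---|---|
| 1 | baseline | none | abstinent or satiated, counterbalanced |
| 2 | baseline, same week | none | the other state |
| 3 | end of week 12 | 12 weeks of varenicline with active or sham tDCS | not specified |

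If the Neuroimaging section's numbering is used instead of time order, scan 2 is the satiated baseline scan. Either way it precedes treatment. With counterbalancing, about half of the chronologically second scans are satiated and half abstinent.

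**Step 2. What would an arm contrast at scan 2 estimate?** For whole randomised arms the true difference is 0, so a two-sided 5% test rejects with probability 0.05 whatever tDCS does.

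The protocol's sentence applies after sorting by outcome, and there the zero is not guaranteed. At 40% and 80%, the sham quitters are 25 × 0.40 = 10 people and the active quitters 25 × 0.80 = 20. If baseline activation predicts quitting, as the same sentence expects, these are differently selected groups. They can differ at baseline with no effect of tDCS on the brain measure.

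**Step 3. Which baseline goes with scan 3?** The cue-reactivity part of Background and Rationale compares pre- with post-treatment scans. The reward-anticipation part and Hypothesis 2 compare with baseline. Outcome Measures uses change in BOLD. None says whether the abstinent or the satiated scan is meant.

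**Step 4. How many scan-3 participants have an undefined state?** Non-quitters in the sham arm: 25 × (1 − 0.40) = 15. In the active arm at 80%: 25 × (1 − 0.80) = 5. This counts people whose recent smoking is not set by the protocol; it does not measure bias. The two-hour smoke-free request in Procedures is written for treatment sessions. The breath and urine tests before scans are for alcohol and other drugs.

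**Step 5. What could smoking status do to the arm contrast at scan 3?** The protocol gives no effect of current smoking on the signal, so I assume a shift of 0.25, 0.5 or 1.0 SD. Smoking status differs between arms by 0.80 − 0.40 = 0.40, so the arm difference arising through smoking status alone is d = 0.40 × shift. With 25 per arm, SE = √(2/25) = 0.283 SD, and the chance of significance is Φ(d/SE − 1.96) + Φ(−d/SE − 1.96).

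| Assumed shift (SD) | d (SD) | Chance of significance |
|---|---|---|
| 0.25 | 0.10 | 6% |
| 0.5 | 0.20 | 11% |
| 1.0 | 0.40 | 29% |

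This is a real consequence of treatment acting through quitting. It affects how an arm difference is interpreted and is not a bias in the randomised comparison.

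**Step 6. Acquisition.** The Neuroimaging section lists task BOLD, resting connectivity, quantitative T1 mapping and DTI. Neither spectroscopy nor perfusion appears.

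**The case against.** The strongest reply is that the sentence is a prediction and not a test specification. It speaks of the result of active treatment, which only a post-treatment scan can show, and it reads like a leftover from a two-scan design (an inference; the protocol does not say so). The planned ANOVA covers groups and time points generally, and the rationale, hypotheses and outcome definition all aim at change. This stands, and it limits the finding. Four stronger readings are tempting, and the protocol does not support them.

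- *The whole imaging question is tested on the wrong scan.* It is not: the third scan is within the ANOVA and the pre/post aims. What is wrong is the one scan named for the directional contrast.
- *Any significant result at scan 2 is a false positive because the truth is zero.* That holds for whole arms only. The sentence conditions on outcome, so selection could produce a genuine baseline difference, which would still not be a tDCS effect.
- *Nicotine state confounds active versus sham at scan 3.* Smoking at week 12 arises after randomisation and may mediate the effect. Confounding describes the non-randomised quitter comparison and, through the choice of baseline, the pre-post change.
- *The ANOVA treats two states as two times.* The protocol never defines the time factor, and its coding may properly be left to an analysis plan.

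It can also be said that state is not wholly unmonitored. Craving, mood and withdrawal are assessed before each scan and related to the MRI measures by regression, and the Abstract has expired CO at each study visit. That helps, but none of it defines the state at scan 3 or records time since the last cigarette.

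**Conclusion.** The point holds in a limited form. Data Analysis names a pre-treatment scan for the expected arm difference, contrary to the Abstract, Design, Eligibility Criteria and Neuroimaging sections, which agree with one another. The comparator for the third scan is unnamed and its smoking state undefined, so the pre-post change and the quitter versus non-quitter comparison are entangled with recent smoking. GSH spectroscopy and perfusion have no listed acquisition.

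The whole-arm difference at scan 2 is exactly zero in expectation. The size of the scan-3 problem cannot be derived from the protocol: the 15 sham non-quitters rest on its assumed 40% rate, and the 6% to 29% range rests on my assumed signal shifts and the 40% and 80% rates.

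This is a should-fix. Imaging serves a secondary objective that the Background calls exploratory, in a 50-person pilot. The primary outcome and the sample size are unaffected. The state information does need settling before week-12 scans are acquired, because a later analysis plan cannot recover it.

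**What to change.** 1. In Data Analysis, replace *second* with *third (end-of-treatment)*, so that the section agrees with Design and Neuroimaging.
2. Specify the imaging comparison as the arm effect at the third scan adjusted for one named baseline scan, or equivalently arm by time on those two scans. Analyse satiated versus abstinent as a separate baseline contrast. Present results within quitters or non-quitters as non-randomised.
3. Record expired CO and time since the last cigarette at the third scan, and account for both in the quitter versus non-quitter comparison. Do not adjust the main randomised arm contrast for them, since they may lie on the causal path. Adjustment will separate quitting from recent smoking only in part, because quitters all have long intervals; the report should say so. Requiring continuing smokers to be scanned after 12 hours' abstinence is not needed: it would replace one state difference with another, acute withdrawal against weeks of abstinence.
4. Reconcile the Abstract, Neuroimaging and Outcome Measures sections on GSH spectroscopy and perfusion, by deleting them or adding the acquisition.

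The cost is wording, some analysis work, and one extra question on the day of the third scan; CO is already planned at study visits. Sample size does not change.
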